**Methods:**

In this superiority randomized controlled parallel trial with single-blind assessment, 60 participants will be allocated to the control group (CG) or the intervention group (IG). The CG will receive specialized nurse-administered foot care, including callus removal, nail care guidance, and self-care education. The IG will receive the same care plus a customized silicone orthosis for toe realignment for 6 months. Assessments will occur at baseline and 3 and 6 months for the primary outcomes (pre-ulcerative lesions and ulcer incidence) and secondary outcomes (pressure distribution, foot function and health, quality of life, safety, and comfort). Two-way ANOVAs (p < .05) will assess group, time, and group by time effects following an intention-to-treat approach.

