### Randomization, allocation, and blinding

2.3

Participants will be randomly allocated to the IG or CG by a random numeric sequence prepared by the WINPEPI software (PEPI-for-Windows) [41] by an independent researcher who will be unaware of the numeric codes for the groups. This sequence will be generated into 16 blocks of four to eight people per block. The numeric sequence will be kept in sequentially numbered opaque envelopes according to the order generated by the software. This sequence will be kept confidential and stored in a location that blind assessors will not have access to. Participants will also be stratified according to the risk classification of ulcers (IWGDF grade 2 and 3 equally distributed). Thus, 30 participants will be stratified to the subgroup with ulcer risk 2, and 30 participants will be stratified to the subgroup with ulcer risk 3, totaling 60 participants.

After agreeing to participate in the study and signing an informed consent form, allocation to the groups will be made by another independent researcher who will not know the numeric code identifying the groups. All personal data will be kept confidential before, during, and after the study by coding the participants’ names. Only the nurse and the person receiving the treatment will know the meaning of the code. After allocation to the IG, digital orthoses will be made, and the participant will be able to pick them up 24 h later.

Due to the characteristics of the intervention, it will not be possible for the nurse responsible for making the orthoses to be blinded. Participants also cannot be masked regarding the intervention since the therapy modality to be applied (toe orthoses) is known to the general public, and the differences between intervention and non-intervention are completely evident. However, participants will not be aware of the study's hypothesis.

The data tabulation of all assessments and statistical analyses will be done by an independent researcher who is blinded to the intervention modality and numerical codes identifying the groups. Before each assessment, all participants will be instructed to not reveal which group they belong to (IG or CG), and this procedure will be reiterated at each new re-assessment.

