### Sample calculation and statistical analyses

2.7

The sample size calculation was performed using GPower v. 3.1 software [47] based on the primary outcome variable of the study: the presence of hyperkeratosis (pre-ulcerative lesions). For this outcome, the relative risk (RR) was calculated based on the incidence of hyperkeratosis after treatment with silicone digital orthoses in people with DPN from a previous study [35] using a contingency table. The sample size calculation used the following parameters: RR = 0.4913, test power = 0.80, α = 0.05, and a chi-squared test for contingency tables, resulting in a sample size of 54 participants. Assuming a 10 % loss to follow-up, 60 participants will be needed.

The inferential statistical analysis will be done by adopting an intention-to-treat approach. The imputation of missing values for the analyzed variables will be depend on the nature of the losses. After confirmation of normality (Kolmogorov–Smirnov test), homoscedasticity (Levene test), and imputation of means for missing data of variables with normal distribution, a two-way repeated measures ANOVA will be performed followed by Newman–Keuls post-hoc test to obtain group (CG and IG), time (baseline and 3 and 6 months), and group by time interaction effects. Significant differences will be considered with an alpha of 5 %. For the description of the intervention effect, the effect size (Cohen's d coefficient) and the difference between means with 95 % confidence intervals will be calculated.

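### The group-by-time ANOVA leaves out the IWGDF-risk stratum and treats baseline as a visit, which costs efficiency but not validity; separately, Newman–Keuls gives no strong familywise control

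*Protocol article*

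**What the plan says.** Section 2.3 of the protocol article makes ulcer risk a stratification factor: "Participants will also be stratified according to the risk classification of ulcers (IWGDF grade 2 and 3 equally distributed", with 30 participants in each stratum.

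Section 2.7 fixes the analysis: "a two-way repeated measures ANOVA will be performed followed by Newman–Keuls post-hoc test", in order "to obtain group (CG and IG), time (baseline and 3 and 6 months), and group by time interaction effects". The abstract names the same three effects: "will assess group, time, and group by time effects following an intention-to-treat approach". Neither place lists a stratum term or a baseline covariate. On the error rate, section 2.7 says "Significant differences will be considered with an alpha of 5" per cent. It states no condition for running the post-hoc tests and no other multiplicity rule.

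The ANOVA is conditional on normality and equal variances, so it is read here as the analysis of the continuous outcomes.

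**The concern.** Three choices are involved.

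- **Stratum.** Randomisation is balanced on a factor that grades the risk of ulceration, but the model does not use it. The between-group error term then carries variation that the design has already balanced.
- **Baseline.** With baseline as a time level, the group main effect includes a visit at which randomisation makes the expected difference zero. The treatment effect has to be read from a 2-df interaction.
- **Post-hoc test.** Newman–Keuls controls familywise error when all means are equal, but not when some truly differ. Both arms receive callus removal and self-care instruction, so a common change over time is plausible.

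At stake are power in a 60-person trial and the credibility of individual post-hoc group differences.

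**Working it through.** **Inputs from the article.** Allocation 1:1 (section 2.1); two strata of 30 (section 2.3); three visits, alpha 0.05, 54 participants before loss and 60 after (section 2.7). The inflation checks: 54 / 0.90 = 60. Per arm: 54 / 2 = 27. The 54 comes from a chi-squared calculation on hyperkeratosis and is taken as given.

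**Assumptions, not in the article.** Group difference of 0.7 SD at 3 and 6 months and none at baseline; equal correlation ρ between any two visits, set at 0.3, 0.5 and 0.7; stratum effects as stated in step 5.

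**1. Group main effect.** Expected difference = (0 + 0.7 + 0.7)/3 = 0.467 SD, two thirds of 0.7. SE = √[(2/27)(1 + 2ρ)/3]. At ρ = 0.5 the SE is 0.222, the ratio 2.10 and power 54%.

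**2. Interaction.** The sum of squared deviations of the visit differences from their mean is 0.467² + 0.233² + 0.233² = 0.327. Noncentrality = (27/2)(0.327)/(1 − ρ) = 4.41/(1 − ρ), on 2 and 104 df.

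**3. Baseline-adjusted 6-month contrast.** SE = √[(2/27)(1 − ρ²)].

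| ρ | Interaction: noncentrality | Interaction: power | Adjusted contrast: SE | Adjusted contrast: ratio | Adjusted contrast: power |
|---|---|---|---|---|---|
| 0.3 | 6.30 | 59% | 0.260 | 2.70 | 75% |
| 0.5 | 8.82 | 75% | 0.236 | 2.97 | 83% |
| 0.7 | 14.70 | 93% | 0.194 | 3.60 | 94% |

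Simulation agrees within about one point: 74% against 82% at ρ = 0.5, and 93% against 93% at 0.7.

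**4. How much of the gap is degrees of freedom.** At ρ = 0.5, √8.82 = 2.97. The interaction therefore carries the same signal as the adjusted contrast, but it needs both follow-ups to reach it and then spreads it over 2 df. A like-for-like comparison at one visit sets change from baseline, variance 2(1 − ρ), against adjustment, variance 1 − ρ². The ratio is (1 + ρ)/2 = 0.65, 0.75 and 0.85, so adjustment is more precise at each of these correlations.

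**5. Stratum.** Simulation with 60 participants, ρ = 0.5 and 6,000 runs:

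- Single follow-up comparison without the stratum: type I error 4.3% for a 0.5 SD stratum effect and 3.1% for 1 SD, both conservative.
- Power at a true 0.75 SD difference and a 1 SD stratum effect: 74.9% without the stratum and 81.9% with it.
- Change from baseline with a stratum effect constant over time: type I error 5.1% and 5.5%, because the effect cancels.
- Lesion incidence by an unstratified chi-squared test, 15 per arm per stratum: size about 3.1% if stratum risks are assumed to be 40% and 80%, and about 1.3% at 30% and 90%.

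**6. Newman–Keuls.** Two groups by three visits give six cell means; this is inferred, since the article does not say which means are compared. A strong common time trend separates them into three CG–IG pairs, each then tested at a full 5%.

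- Bound if independent: 1 − 0.95³ = 14.3% for three pairs; 1 − 0.95² = 9.75% for the two follow-up pairs.
- Three pairs simulated at 5% each (40,000 runs; ρ = 0.3, 0.5, 0.7): 13.8%, 12.6% and 11.0%. Follow-up pairs only: 9.5%, 9.2% and 8.3%.
- Gated on a significant interaction when none exists, pooled error term: 1.3% to 3.0%.
- Gated, groups truly differing at 6 months only: about 7–10%. The two null pairs are then baseline and 3 months, so this figure counts the baseline pair.

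**The case against.** The defence has four parts.

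- **The model is conventional and valid.** This stands. The interaction F-test kept a size near 5% in simulation, including with a 1 SD stratum effect omitted. A reader might infer that baseline is ignored; it is used, but inefficiently. The 54% power of the group main effect is not the power of the plan, because the interaction is also specified.
- **Post-hoc tests normally follow a significant interaction.** This is a fair reading of "followed by Newman–Keuls post-hoc test", and under it the error is at or below about 5% when there is no interaction. The article does not state the gate, however, and gating does not give strong control once an interaction is real.
- **The stratum omission does not inflate error.** Correct. A reader might take all three features as reasons why 5% is not held, but only Newman–Keuls bears on that.
- **Covariates belong in the analysis plan.** This holds only in part. The article names a two-way model and lists its terms, so a fuller plan would have to depart from that list to add the stratum or a baseline covariate.

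A reader might also infer much larger error rates if the within-subject error term were used for group comparisons. The article does not say which error term applies, so that reading is not relied on.

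**Conclusion.** The point holds as one of efficiency, with a separate and modest weakness in the post-hoc step. The documents do not support a claim that the main analysis is invalid or that the plan as a whole misses its 5% level.

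- Power is lost against a baseline-adjusted contrast: about 16 points at a correlation of 0.3, 8 at 0.5 and almost none at 0.7, on an assumed 0.7 SD effect at both follow-ups. Part of this is 2 df against one.
- Omitting a prognostic stratum makes the group main effect and single-visit comparisons conservative. A stratum effect constant over time leaves the interaction test unaffected.
- Ungated Newman–Keuls, with a common time trend and no treatment effect, gives about 8–9% over the follow-up visits, or 11–14% counting baseline. The baseline pair cannot produce a false efficacy claim, so the lower range is the relevant one.

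The correlations, effect size and stratum effects are all assumptions. The Newman–Keuls figures also assume complete separation of the visits, or a pooled error term where gated.

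**What to change.** In section 2.7, for continuous outcomes:

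1. Fit a mixed model to the 3- and 6-month values, with baseline value and IWGDF stratum as covariates and group, visit and group by visit as effects.
2. Name the 6-month IG–CG contrast, with its 95% confidence interval, as the main contrast for each outcome.
3. Remove Newman–Keuls; if the 3-month contrast is also tested, apply Holm to the two.
4. Include the IWGDF stratum in the between-group analysis of lesion incidence.

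The cost is wording only. Baseline values and risk class are already collected, the article reports the trial as still recruiting, and neither the sample size nor any visit changes.

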### Data management

2.8

The study steering committee is comprised of one undergraduate student (responsible for blind assessment, data tabulation, and codification), one senior researcher (responsible for data acquisition and monitoring data tabulation), one coordinator (responsible for managing the project), and one assistant researcher (responsible for the recruitment and scheduling of collections). All information collected during the protocol will be entered into an electronic form by those responsible for data collection. All information will be collected on physical and electronic forms by those responsible for data acquisition who are blinded to the participants’ allocation. The integrity and validity of the data will be verified at the time of data entry (edit checks). Identification of potential recruits will be done by the project manager and the research assistant. The research assistant will be trained on how to approach the eligible subjects during the initial recruitment contact for the survey (made by phone calls) and how and when to contact them for follow-up and data collection. After study completion, anonymized data will be published in the public USP repository (https://repositorio.usp.br/).

### Data supervision and monitoring

2.9

The data monitoring committee (steering committee) and the Faculdade de Medicina da Universidade de São Paulo Board will regularly monitor (depending on the recruitment numbers and collections performed) the study datasets and make recommendations on necessary protocol modifications or termination of all or part of the study. A trimester meeting will be held to facilitate the study's development. All team members can request meetings as needed. All adverse events occurring during the clinical trial period will be recorded. The patients will be advised to report any discomfort and foot pre-ulcerative signs (e.g., blisters and calluses) or foot ulcers to the main researcher, who will ask for the blinded podiatrist nurse to assist the patient.

## Discussion

3

This paper describes a randomized trial protocol that aims to evaluate the efficacy and safety of customized silicone digital orthoses in preventing ulcers, pre-ulcerative lesions, and peak pressures during gait in people with DPN and risk category 2 or 3. This study is supported by evidence that people with DPN often develop calluses due to toe misalignment and increased plantar pressure. If toe deformities and calluses are not addressed in a timely manner, they can evolve into plantar ulcerations [25,33,48]. Once installed, these ulcerations are difficult to manage and have the potential for amputation. Therefore, early prevention and treatment are crucial.

Conservative treatment for dealing with calluses, including debridement, is the first clinical choice; however, when that fails, surgical treatment is the alternative [49]. Although conservative treatment provides quick relief for patients, it is of limited benefit because if plantar pressure at the forefoot is not redistributed effectively, the callus will soon form again as a way of protecting against chronic excessive mechanical stimulation [50]. Therefore, callus removal must be accompanied by strategies for redistributing plantar pressure. Customized silicone orthoses are a strategy for toe realignment and, consequently, plantar pressure redistribution. A single clinical trial has indicated the efficacy and safety of using customized orthoses at the forefoot to reduce the incidence of pre-ulceration lesions in people with DPN [35]. In addition, other studies have evaluated the use of silicone orthoses aimed at reducing peak pressure with promising results [[36], [37], [38]]. Although the use of silicone orthoses is recommended by the IWGDF guidelines [32], its use worldwide is limited due to a lack of evidence. Thus, a randomized controlled trial addressing the effectiveness of this approach to prevent ulcerations and pre-ulcerative lesions would provide more consistent evidence for the adoption (or not) of this approach as a preventive strategy for people with DPN.

### Trial status

3.1

The overall status of the trial is currently recruiting patients for the study.

## Data Availability

No data was used for the research described in the article.
